## Methods

### Study Design

The study will use a quasi-experimental, mixed methods design to assess the feasibility, usability, and acceptability of the tool (Multimedia Appendix 1). There will be two treatment groups: no use of the tool (standard care only, SC) and use of the tool (standard care plus, SC+). Survivors mostly come to the site through the organization’s crisis hotline. A survivor calls the hotline for help, and if deemed appropriate, the site makes an appointment for an intake interview to determine the survivor’s needs, including housing. Subsequently, a case manager is assigned to meet with the survivor. For new clients, the meetings normally take place twice a week during their first month. In these meetings, the case manager helps the survivor apply for a myriad of benefits, including housing programs if housing has been identified as a need. The meeting frequency then lessens as the survivor’s needs are met. SC will consist of no tool use, in or outside of the case manager meetings. SC+ will consist of tool use, in or outside of the case manager meetings. To ensure access to the tool regardless of whether a meeting is scheduled during the study period, the study team will email all SC+ participants a link to the tool for their self-use.

Following a historical cohort control group design, the study team will recruit participants into each arm, sequentially. We will recruit SC participants first. After all SC participants have completed their follow-up surveys, SC+ recruitment will begin. The SC and SC+ study groups will engage in two data collection points: one baseline survey prior to the housing meeting and one follow-up survey 2 weeks after completion of the baseline survey, each anticipated to take up to 30 minutes to complete. Study participants will be given a 1-week grace period to complete each survey. During SC+, the study team will email the tool to all enrolled participants following the completion of their first survey.

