The study team had initially considered a randomized controlled trial (RCT) but selected a quasi-experimental, historical cohort design for several reasons. First, randomizing at the participant level, as in an RCT, was not feasible. Randomizing participants would have required the case managers to know the participant’s enrollment status and arm assignment to introduce the tool to the appropriate person. This lack of concealment could have produced differential treatment by the case managers based on the participant’s enrollment status. Second, we anticipated that tracking each participant’s arm assignment in an RCT would have added to the staff’s already limited capacities, a concern that the site also shared. Third and final, there was the concern that SC+ participants could interact with SC participants and share the tool, further confounding the results. Fortunately, the current historical cohort control group design mitigates the above risks. In the current design, case managers deliver SC, followed by SC+, regardless of whether a participant enrolls, thereby reducing any potential administrative burden on the staff. While the case managers are not entirely blinded to the participants’ enrollment status and arm assignment, the current design reduces the risk by emailing participants directly with the intervention link. If a participant mentions the link to the case manager, then the case manager will know that they have signed up for SC+. Otherwise, case managers will not know and will be encouraged to share the tool with all clients. Furthermore, the tool will only be accessible to participants during the SC+ arm, hence removing the possibility of participants interacting with the tool during the SC arm. To mitigate ethical concerns over one group and not the other receiving the tool, all SC participants will receive access to the tool after the SC+ arm completes data collection. Thus, while the study team had considered an RCT, the quasi-experimental, historical cohort control group design ultimately allowed the study team and partner site greater logistical flexibility, decreased administrative burden, and lower risk of confounding.

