### Procedures

The two sequential study arms will follow the same procedures, differing only in treatment (Figure 2). In each arm, the program director will send a mass email about the study to their clients with the recruitment flyer and screening form link. The case managers may also refer prospective participants to the study in their individual meetings. If the prospective participant is interested, they will answer questions on a digital form to determine whether they meet the inclusion criteria. If the prospective participant meets all the inclusion criteria, the form will automatically collect their contact information, which will then trigger a digital consent form that will be emailed to the participant. If the prospective participant wishes to join the study after reading the consent form, they will click yes to proceed to the baseline survey. As we are waiving the collection of a signature to protect the participant’s confidentiality, clicking yes will constitute the participant’s consent to join the study. Should the participant proceed, they will receive the baseline survey immediately and a follow-up survey 2 weeks later, both by email. Each survey will be active for 1 week, and up to 3 email reminders will be sent to the participant during the 1-week grace period if the survey remains incomplete. If the participant completes the follow-up survey during the grace period, they will receive an additional email upon completion with the answer key to the knowledge quiz.

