### Statistical Analysis

Multiple linear regression models will be used to test the difference-in-difference in means of housing knowledge, housing self-efficacy, and staff trust. The inclusion of independent variables in the models will be determined by prior tests assessing whether any significant differences exist in outcome variables by demographic and moderating variables. The outcomes of interest will also be input as independent variables to determine the association between housing knowledge, housing self-efficacy, and staff trust.

Sample size, the rates of recruitment, retention, and response, and timeline will be recorded. Ease of implementation and outcome appropriateness will be collected through open-ended questions in individual interviews with the key informants, while acceptability and perceived usability will be collected through a mix of Likert scale and open-ended questions in the surveys and interviews.

To analyze the qualitative data, the written answers from the participant surveys and the transcripts from the key informant interviews will be inductively coded using a constant comparative method. Two coders will separately code the transcripts and then compare and iterate for agreement. Interrater reliability will be calculated as the number of codes in agreement, in proportion to the total number of codes [45]. We will iterate our codes until we achieve a minimum 80% agreement on 95% of our code set [45].

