## Results

Recruitment for the SC arm began in March 2022 and completed in April 2023. Of the prospective participants, 75 participants were screened, 44 participants were deemed eligible, 35 participants were enrolled (ie, consented to the study), and 23 participants completed both baseline and follow-up surveys. Initially, we had sought to attain 50 completed surveys, 25 in each arm. However, the recruitment timeline for SC took longer than anticipated, and the enrollment numbers were lower than expected. Following 1 year of recruitment for SC that resulted in 23 completed surveys, we sought to expedite the recruitment timeline for SC+. Recruitment for the SC+ arm started in January 2024 and is anticipated to end by May 2024. After SC+ arm recruitment ends, we plan to recruit, conduct, and complete the key informant interviews in June 2024. We subsequently expect to complete the study and be ready to analyze the results by the end of June 2024.

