### Future Directions

#### Considerations

When implementing the SC arm, the study team encountered several delays with data collection that have been highlighted here for future consideration.

To start with, the study was conducted during the pandemic, at a time when nonprofits, like the partner site, were experiencing significant labor shortages and funding constraints [49,50]. At the same time, demand for services continued to increase, leading more nonprofits to report a decrease in their ability to provide services [51]. As such, the study’s data collection efforts often inadvertently competed with the staff’s full workload. In turn, the crisis context of domestic violence work also may have prevented the staff from fully participating in the study as they had hoped.

Further delaying data collection were unanticipated enrollment issues. Halfway through SC recruitment, we discovered about half of the SC participants were not truly eligible for the study. We infer that some participants had forwarded the study information to friends and family, who then falsely answered the screening questions to participate in the study. While we subsequently removed those faulty participants, we also extended the SC recruitment timeline to make up for the loss.

Finally, the study team had not accounted for the time it would take to obtain the appropriate site approvals, nor had we prepared for an unexpected change in case management systems.

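### The historical-control design is credited with a lower risk of confounding, but arm coincides exactly with calendar period, so the difference-in-difference cannot separate a tool effect from a period difference in the 2-week change

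*Protocol article*

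**What the plan says.** Study Design sets out the allocation: "Following a historical cohort control group design, the study team will recruit participants into each arm, sequentially". SC+ recruitment opens only after every SC participant has finished follow-up. The section explains why an RCT was rejected and closes by crediting the chosen design with "greater logistical flexibility, decreased administrative burden, and lower risk of confounding". The one place in that argument where confounding is explained is the worry that "SC+ participants could interact with SC participants and share the tool, further confounding the results".

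Results gives the dates. SC recruited from March 2022 to April 2023 and yielded 23 completers against a target of 25 per arm. For the second arm: "Recruitment for the SC+ arm started in January 2024 and is anticipated to end by May 2024".

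Statistical Analysis states: "Multiple linear regression models will be used to test the difference-in-difference in means of housing knowledge, housing self-efficacy, and staff trust". Covariates are to be chosen by prior tests on demographic and moderating variables; calendar period is not named.

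Three parts of the plan use the between-arm contrast: research question 1 (initial treatment effect), Stop criterion 1 in Feasibility Criteria, and the full-trial sample size, which is to be based on the effect sizes found here. Limitations names incomplete blinding of case managers and the specific setting. It does not mention calendar period.

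**The concern.** An RCT balances the arms over calendar time; a historical control does not. The chosen design reduces contamination between arms, and in exchange it makes arm and period the same variable. Describing that exchange as a lower risk of confounding credits the design with a property it lacks.

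The difference-in-difference label can hide this. In its usual form both groups are observed over the same dates, so a shared period effect cancels. Here no SC participant is observed in the SC+ window. If two weeks of standard care achieve more, or less, in 2024 than in 2022–23, the difference is counted as a tool effect.

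The stake is what the study may conclude. The contrast is to be reported as an initial treatment effect, is one of two conditions for proceeding, and sets the size of the next trial.

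**Working it through.** **1. Gap between the arms.** Only months are given, so the range is:
- Shortest recruitment gap: 30 April 2023 to 1 January 2024 = 246 days; 246 / 30.44 = 8.1 months.
- Longest: 1 April 2023 to 31 January 2024 = 305 days = 10.0 months.
- Data collection: the last SC follow-up could fall up to 4 weeks after recruitment (1 week for baseline, 2 weeks' interval, 1 week for follow-up). The shortest gap is then 246 − 28 = 218 days = 7.2 months.

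Overlap is zero in every case.

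**2. What the model can identify.** Let *c1* and *c2* be the mean 2-week change under standard care in the SC and SC+ periods, and *t* the tool effect.
- Expected change in SC = c1; in SC+ = c2 + t.
- Difference-in-difference = t + (c2 − c1).

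Stable baseline level differences cancel, but c2 − c1 does not. In matrix terms, the model with intercept, arm, time and arm-by-time has 4 columns and rank 4. Adding period and period-by-time gives 6 columns, and the rank stays 4: period equals arm, and period-by-time equals the treatment term. Adjusting for measured client characteristics can reduce differences in client mix, but cannot separate period from arm.

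**3. Illustration for Stop criterion 1.** The plan gives no figure to reproduce. Assumptions: no tool effect; 23 SC completers (Results) and 25 SC+ completers (the original target); three independent outcomes, all shifted equally; normal approximation; shift *d* = c2 − c1 in SDs of the change score. The plan does not define how near to significance counts, so two readings are shown: positive with two-sided p<0.10 (critical z 1.645) and positive with one-sided p<0.10 (critical z 1.282).

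- SE = √(1/23 + 1/25) = 0.289
- P(one outcome) = P(Z > z − d/SE)
- P(at least one of three) = 1 − (1 − P)³

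| Shift d | One outcome, two-sided | Any of three, two-sided | One outcome, one-sided | Any of three, one-sided |
|---|---|---|---|---|
| 0 | 0.050 | 14% | 0.100 | 27% |
| +0.2 SD | 0.170 | 43% | 0.278 | 62% |
| +0.3 SD | 0.272 | 61% | 0.404 | 79% |
| −0.2 SD | 0.010 | 3% | 0.024 | 7% |

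Worked cell: d = 0.2, two-sided: 1.645 − 0.2/0.289 = 0.953; P = 0.170; 1 − 0.830³ = 0.43.

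The d = 0 row reflects testing any of three outcomes at a loose threshold and has nothing to do with period. The effect of period is the change from that row.

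**4. Illustration for the next trial's sample size.** Per arm, two-sided 5%, 80% power: n = 2(1.96 + 0.842)² / δ². For δ = 0.3 SD, n = 175; for δ = 0.5 SD, n = 63. A true effect of 0.3 SD with a period shift of +0.2 SD would have an expected estimate of 0.5 SD and point to 63 per arm where 175 are needed. A shift the other way would inflate the sample size.

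**The case against.** The best defence is that the disputed phrase sums up the risks just listed. The section uses confounding to mean tool sharing, and on contamination the design does do better than an RCT. The design is openly called quasi-experimental and historical, the primary objective is feasibility, and Hypothesized Findings looks mainly at direction. This stands as an account of what the authors meant. It does not rescue the sentence as a general comparison with an RCT, and it does not explain why Limitations omits period.

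Several stronger readings are tempting, and the documents do not support them:

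- *That the protocol claims protection against period effects.* It says nothing about calendar time. The fault is an unqualified claim and an omitted limitation.
- *That Procedures asserts comparable groups.* "The two sequential study arms will follow the same procedures, differing only in treatment" describes procedures and itself calls the arms sequential. It needs no correction.
- *That standard care is shown to have been weaker during SC.* Considerations reports that "the study was conducted during the pandemic, at a time when nonprofits, like the partner site, were experiencing significant labor shortages and funding constraints", and of the delays, "nor had we prepared for an unexpected change in case management systems". These are given mainly as causes of delayed data collection, and the system change is undated. They make a period difference plausible without fixing its direction. Background also reports DHS shelter numbers well above prepandemic levels, and a harder housing environment could work against SC+.
- *That a period shift alone yields a Go.* A Go also requires that Stop criterion 2, on survivors' intent to continue use, is not met, and it leads only to a further, fully powered trial.
- *That criterion 1 plainly lets a fall in SC count.* It can be read as already requiring a rise in SC+; the wording leaves this open.

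**Conclusion.** The point holds in this form: arm is fully aliased with calendar period, the planned analysis cannot separate the two, the claim of lower confounding risk is true only of contamination between arms, and Limitations omits the problem. This follows from the recruitment dates and the sequential rule and needs no assumption.

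The size cannot be known from the documents. On the assumptions above, a 0.2 SD shift favouring SC+ takes the chance of passing criterion 1 without any tool effect from 14% to 43% (two-sided reading) or from 27% to 62% (one-sided reading); an equal shift the other way takes it to about 3% or 7%. Correlated outcomes or fewer SC+ completers would change these figures. They show sensitivity and are not estimates of bias.

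**What to change.** 1. **Study Design and Limitations.** Replace the claim about confounding with: *lower risk of contamination between arms, at the price of confounding of arm with calendar period*. Add the same point to Limitations.
2. **Statistical Analysis and the sample size section.** Report each arm's pre-post change with a 95% CI beside the between-arm difference, and describe that difference as not attributable to the tool alone. Carry the same caveat into the full-trial sample size estimate.
3. **Feasibility Criteria, Stop criterion 1.** State that an outcome counts only if SC+ itself rises from baseline. This closes the route through a fall in SC. It does not guard against a period improvement in standard care, which would also raise SC+; that is why items 1 and 2 are still needed.

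A regression of the SC 2-week change on enrolment date is optional: with 23 people it is imprecise, and it cannot be extrapolated across the gap. Comparing baseline levels would add little, because the difference-in-difference already removes stable level differences.

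The cost is wording and a few descriptive estimates from data already planned, with no new participants. The price is a more modest statement about the tool's effect.

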### Study Population

The partner site, a community-based domestic violence program based in New York City, provides domestic violence and sexual assault counseling, case management, legal services, occupational therapy, and support groups for any survivor of domestic violence and is particularly attuned to the needs of survivors who are D/deaf or Hard of Hearing or have a disability [30]. Based on the last set of data collected by the site in 2021, the partner site, on average, served 171 new and existing clients per month. About 26% (n=45) of clients were new to the program each month. Of those who disclosed their information to the site, 84% (109/130) identified as a cisgender woman, and 15% (19/130) as a cisgender man. The majority identified as either Black (48/114, 42%) or Latino/a/x (32/114, 28%). None chose to disclose their employment status, but more than half (76/151) reported being on some form of public assistance. Finally, 52% (66/128) of clients reported a mental health disability, 18% (23/128) reported a sensory disability (ie, blindness or deafness), 17% (22/128) a physical disability, 10% (13/128) a medical condition, and 3% (4/128) a cognitive disability. The site has three full-time case managers, who cover a wide range of survivor needs including housing, and a full-time program director and assistant director who oversee the case managers.

### Eligibility Criteria

Survivors, or participants, will be eligible for study inclusion if they consent to participate; are seeking assistance from the site at the time of joining the study; are at least 18 years old; have access to a device with web-browsing capability (eg, smartphone, tablet, or the site’s computers); are looking for housing; have a safe email account, with “safe” being interpreted as the survivor sees fit; can read English without assistance from others including translation or interpretation assistance; and have not participated in the study before. Staff, or key informants, will be eligible for inclusion in the study if they give oral consent to participate, are at least 18 years old, and bear the title or responsibilities of “case manager” or “director.” We expect to recruit five key informants.

### Procedures

The two sequential study arms will follow the same procedures, differing only in treatment (Figure 2). In each arm, the program director will send a mass email about the study to their clients with the recruitment flyer and screening form link. The case managers may also refer prospective participants to the study in their individual meetings. If the prospective participant is interested, they will answer questions on a digital form to determine whether they meet the inclusion criteria. If the prospective participant meets all the inclusion criteria, the form will automatically collect their contact information, which will then trigger a digital consent form that will be emailed to the participant. If the prospective participant wishes to join the study after reading the consent form, they will click yes to proceed to the baseline survey. As we are waiving the collection of a signature to protect the participant’s confidentiality, clicking yes will constitute the participant’s consent to join the study. Should the participant proceed, they will receive the baseline survey immediately and a follow-up survey 2 weeks later, both by email. Each survey will be active for 1 week, and up to 3 email reminders will be sent to the participant during the 1-week grace period if the survey remains incomplete. If the participant completes the follow-up survey during the grace period, they will receive an additional email upon completion with the answer key to the knowledge quiz.

**Figure 2 figure2:**
[figure not shown]
Participant flow. SC: standard care only; SC+: standard care plus.

During the 2-week period between the baseline and follow-up surveys, the participant will receive services as usual in the SC arm and services plus the tool in the SC+ arm. Regardless of whether a participant completes the surveys, the site will continue to provide services to the participant. In the SC+ arm, the study team will email the participant a link to the tool to use over the 2-week treatment period. The case manager will also share the tool in their individual meetings with SC+ participants. If there happens to be no meeting during a participant’s enrollment in the study, the participant can still access the tool through the study team’s email.

For each completed survey, the participant will receive a US $10 Visa eGift card via email for a potential total of US $20 for two completed surveys. Study data will be collected and managed using REDCap (Research Electronic Data Capture; Vanderbilt University) electronic data capture tools hosted at Johns Hopkins University [31,32]. REDCap is a secure, web-based software platform designed to support data capture for research studies, providing (1) an intuitive interface for validated data capture, (2) audit trails for tracking data manipulation and export procedures, (3) automated export procedures for seamless data downloads to common statistical packages, and (4) procedures for data integration and interoperability with external sources.

